## **Other outcomes**

Wearable devices will detect the frequency of protective behaviors associated with fear-avoidance and catastrophizing. A decrease in these behaviors indicates reduced fear of movement and pain-related catastrophizing.

An adverse event is defined as any issue involving the lower back or other parts of the body that the participant perceives to be related to the trial, meeting one of the following criteria: i) that caused the participant to seek medical care for at least two days; and ii) that made their pain or impairment worse. After the intervention, participants will be surveyed regarding any adverse events.

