## ***Interventions***

The physiotherapists who delivered the intervention in both two groups will not be involved in the outcome measures and are not blind to the group assignment. The two groups will conduct an 8-week intervention, for a total of 24 sessions. The interventions in both groups will be completed over 8 weeks, following the 2020 clinical practice guidelines of the North American Spine Association. Subjects will be encouraged to participate in the intervention and assessment throughout the trial protocol. Frequency of attendance, medication changes, adverse events, etc. will be reported by the participants to the physiotherapist in charge of the trial management and will be duly recorded in the case report form.

All participants will use the same version of the app throughout the trial. If a participant's condition worsens during treatment, they may seek other treatments (e.g., pharmacotherapy, physical therapy), but additional exercise therapy is prohibited. Participants must accurately report any extra treatments to the investigator, who will document them in the case report forms. To enhance adherence to intervention protocols, a weekly group WeChat video session will be held. This group-based health coaching allows participants to exchange peer support and psychological encouragement, thereby strengthening engagement between therapists and patients.

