### ***Data management and auditing***

Data will be collected both on paper and electronically. If participants return for follow-up, they will complete paper questionnaires; otherwise, they will use online forms. Paper surveys will be administered by an assessor who has received standardized training, and patients will also fill out their own paper questionnaires. Online surveys will be delivered through a designated app, and TUG testing will be conducted via video conferencing. Both groups may be provided with wearable devices for home use, which will be collected at the end of the intervention. A statistician not involved in the trial intervention will retrieve wearable device data, which two data administrators will then enter into anonymized databases equipped with logic checks (e.g., mandatory fields, response limits). These data will be organized into tables for statistical analysis. During recruitment, patients will receive comprehensive information about the trial's requirements and design, and they may withdraw at any time without giving a reason. Their progress will be tracked using a quality form, and those who drop out or discontinue the intervention will also have outcome data collected. Outcome assessors will document experimental procedures and data on a case report form, assigning each participant a unique code to protect privacy; only the assessors and the corresponding author will have access to these forms. All data entries will be verified twice by two independent assessors, after which the entries become non-editable. A Data & Safety Monitoring Committee is not required, given the low-risk interventions and the minimal likelihood of serious adverse events (incapacitating, life-threatening, hospitalization, or death). Auditing will involve on-site visits by independent supervisors twice a month to verify the presence and accuracy of investigation files, as well as checks on 20% of participants chosen at random to review source data, inclusion and exclusion criteria, missing scales, reporting, and informed consent.

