## **Provisions for post-trial care**

If risks arise during treatment, the project team will address study-related adverse events at the participant’s expense. Should a serious adverse event be deemed related to the clinical research, the project team will cover the necessary treatment costs. Participants who can provide legally valid evidence of loss will receive appropriate financial compensation, including a 300-yuan subsidy for travel and housing expenses.

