| characteristics                                |                 |                                   |   |   |   |
| Pain intensity                                 | Self-reported   | NRS                               | √ | √ | √ |
| Physical function                              | Self-reported   | RMDQ                              | √ | √ | √ |
|                                                | Walking ability | TUG                               | √ | √ | √ |
| Quality of life                                | Self-reported   | SF-12                             | √ | √ | √ |
| Psychopathological symptoms                    | Self-reported   | DASS21                            | √ | √ | √ |
|                                                | Self-reported   | EARS                              | - | √ | √ |
| Exercise compliance                            |                 | Movement completion rate          |   |   |   |
| Fear-avoidance in exercise & catastrophization | Events          | Frequency of protective behaviors | √ | √ | √ |
|                                                |                 |                                   |   |   |   |
| Adverse Events                                 | Self-reported   | -                                 | - | √ | √ |

621

622

623 **Notes:**

624 **Abbreviations:** LBP, Low Back Pain; CLBP, Chronic Low Back Pain; RCTs, Randomized  
625 Controlled Trials; TG, Trial Group; CG, Control Group; FITT-VP, Frequency, Intensity, Time, Type,  
626 Volume, Progression; IMUs, Inertial Measurement Units; RPE, Rating of perceived exertion; NRS,  
627 Numerical Rating Scale; RMDQ, Roland Morris Disability Questionnaire; TUG, Time up and go;  
628 SF-12, 12-item Short Form Health Survey; DASS21, Depression-Anxiety-Stress Scale; EARS,  
629 Exercise Adherence Rating Scale; SPIRIT, Standard Protocol Items: Recommendations for  
630 Interventional Trials; BMI, Body Mass Index; ITT, intention-to-treat; PP, Per-Protocol; SD,  
631 Standard Deviation; MCID, Minimum Clinically Important Difference

632

633

634 **Figure Legends**

635

636 Figure 1. Flow chart of the study

637 Figure 2. Intervention process at first visit.

638

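### The adverse event definition depends on the unblinded participant's own attribution and does not align with the protocol's serious event categories or its later relatedness judgement

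*Protocol*

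**What the plan says.** Other outcomes defines an adverse event as "any issue involving the lower back or other parts of the body that the participant perceives to be related to the trial". The event must also qualify under a second test, "meeting one of the following criteria: i) that caused the participant to seek medical care for at least two days; and ii", where the second item is that pain or impairment got worse.

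Three places describe collection, and all rely on the participant:
- Interventions: "adverse events, etc. will be reported by the participants to the physiotherapist in charge of the trial management", with entry in the case report form.
- Other outcomes: "After the intervention, participants will be surveyed regarding any adverse events".
- Table 3: the row "Adverse Events" is marked self-reported, at 4 and 8 weeks.

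Two other sections use different concepts. Data management and auditing dispenses with a monitoring committee partly because of "the minimal likelihood of serious adverse events (incapacitating, life-threatening, hospitalization, or death"; those categories carry no condition about what the participant thinks. Provisions for post-trial care says: "Should a serious adverse event be deemed related to the clinical research, the project team will cover the necessary treatment costs". Relatedness is there something decided about an event after it is known.

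**The concern.** Causality is normally assessed once an event has been recorded. Here a form of it sits inside the case definition, and the assessor is the participant, who is not blinded (Randomization and blinding). An event the participant puts down to something else is not an adverse event in this trial, however severe.

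Two things are at stake. The first is completeness: the events that matter most for safety are not clearly within the definition, and the protocol states no separate route for them. The second is comparability. The trial group has a weekly therapist-led video session, so that eight of its 24 sessions are supervised. The control group trains alone for all 24 and gets no further instruction unless it asks. The Introduction itself says that unsupervised exercise raises the risk of injury, so harm by arm is a question the protocol raises. Participants with such different contact may differ both in how readily they link an event to the trial and in how often they are prompted to mention it.

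There is also a practical consequence. Under Provisions for post-trial care, the relatedness judgement on a serious event decides whether the project team pays for its treatment.

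**Working it through.** No arithmetic applies. The protocol gives no expected adverse event rate and no attribution rate, so the check is a comparison of its sections.

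**Step 1. Conditions for an event to count (Other outcomes).** (a) The participant perceives it as related to the trial. (b) It led to seeking care for at least two days, or it worsened pain or impairment. Condition (b) is introduced as *one of* two items, but the items are joined by *and*. The introductory phrase favours *either*.

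**Step 2. Apply these conditions to the list in Data management and auditing:** "serious adverse events (incapacitating, life-threatening, hospitalization, or death".
- *Death.* The participant who died can neither attribute the death to the trial nor report it. Condition (a) cannot be met.
- *Hospitalization or a life-threatening event blamed on something else.* Condition (a) fails, so it is not an adverse event.
- *Incapacitating event.* The participant may be unable to attribute or report it, so meeting (a) is uncertain.
- *A one-day admission that the participant does link to the trial, without worse pain or impairment.* Condition (a) is met but (b) fails on either reading.

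Each category on the serious list can therefore contain events that fall outside the definition.

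**Step 3. Compare with Provisions for post-trial care.** If every adverse event is already perceived as related, speaking of study-related adverse events, and of a serious event later deemed related, adds a second attribution by an unnamed assessor. If serious events are instead meant to be identified independently of the participant's view, the protocol does not say who identifies them or where they are recorded. On either reading the sections do not align.

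**Step 4. Look for another route.**
- Interventions: extra treatments must be reported and documented, with no attribution test. The rule follows a sentence about a worsening condition and does not classify what prompted the treatment as an adverse event.
- Criteria for discontinuing: the physiotherapist asks for the reason for withdrawal. This could reveal an event but does not classify it or send it for a relatedness judgement.
- Data management and auditing: outcome data are also collected from those who drop out or discontinue. Adverse events remain self-reported under the same definition.

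No section of the protocol states that serious events are captured regardless of attribution.

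**Step 5. Arm dependence.** Participants know their group, and the two arms differ in therapist contact. The probability that an event is perceived as related, and then reported, may differ by arm. The protocol does not let one say in which direction.

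**The case against.** The strongest reply is that the sections can be read together. The serious categories are listed on their own terms, and relatedness is judged separately under Provisions for post-trial care. On that reading the definition in Other outcomes governs only an *other* outcome, borrowed with a citation from another physiotherapy trial's protocol, and serious events are handled in parallel. Extra treatments and withdrawal reasons would bring many events to light. Data collection details are in Supplemental Material II, which was not available for this review and may already ask about admissions.

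Much of this stands, and it rules out several stronger readings that a reader might infer:
- *Only events the participant has already called related reach the later judgement.* No section says so, and the wording on serious events allows a separate assessment.
- *The trial cannot report serious harm.* The supported statement is that it does not say how serious events are captured.
- *Psychological deterioration goes unrecorded.* The DASS21 is completed by everyone at baseline, 4 and 8 weeks, so such change is measured in both arms whatever its perceived cause.
- *The missing monitoring committee is undermined.* That decision is a prospective judgement about low-risk interventions, not a hypothesis to be tested in 78 participants.
- *A particular share of events will be lost, or a particular false ratio between arms will appear.* Any such figure would only return the rates assumed for it.

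The *one of* and *and* conflict is a drafting slip and adds little weight. What the reply does not supply is a stated rule for capturing serious events regardless of attribution; a citation for the definition does not reconcile the three sections.

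**Conclusion.** The concern holds as a misalignment between three sections of the protocol. Other outcomes makes the unblinded participant's perception an entry condition; Data management and auditing lists serious events without it; Provisions for post-trial care puts relatedness later. Under the stated definition some deaths and admissions are not adverse events, and nothing in the protocol guarantees that they are captured another way. The resulting record may be incomplete, and the comparison of harms between arms may be biased in a direction that cannot be predicted.

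The size cannot be quantified from the protocol. The conclusion assumes that the definition is applied as written and that Supplemental Material II does not already contain an unconditional question on serious events; if it does, the gap narrows to inconsistent wording. The primary outcomes are unaffected. This should be corrected because the change is cheap and events missed during the trial may not be recoverable later.

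**What to change.** Reconcile Other outcomes, Data management and auditing, and Provisions for post-trial care:

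1. Define an adverse event as any untoward occurrence from randomisation to week 8, regardless of perceived cause.
2. State that the serious categories already listed are always captured, whatever the duration of care sought, and say how a death or an admission comes to the team's notice when the participant cannot report it.
3. Record seriousness and relatedness as separate fields. Name who judges relatedness, and keep the participant's own view as one item.
4. Keep the present two criteria, if wanted, only to grade events, and settle whether either or both must be met.
5. Report all-cause, related and serious events by arm.

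The cost is revised wording and a few more fields, collected at the 4- and 8-week assessments already scheduled. More minor unrelated events will be recorded and the adverse event count will look less favourable. No treatment or visit changes.

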## ***Criteria for discontinuing or modifying allocated interventions***

If a participant opts to withdraw from the trial prematurely, the physiotherapist will promptly contact them to determine the reason for withdrawal. Participants who exit the trial, become unreachable for over two weeks, and fail to complete the outcome evaluation will be categorized as dropouts.

- 1) Patients desiring to cease participation.
- 2) Patients unable to undergo the baseline assessment.
- 3) Patients failing to complete the app-based exercise therapy sessions.
- 4) Patients experiencing exacerbated symptoms.

## ***Sample size***

The sample size was calculated using G\*Power 3.1.9 under the following conditions: based on Cohen's standard for effect sizes, 0.2, 0.5, and 0.8 indicate small, medium, and large effects, respectively. A value of 0.3 was selected to represent a small-to-medium effect size, drawing on Murtezani's findings. With  $\alpha = 0.05$ , power = 0.8, and a correlation among repeated

measures of 0.5, a two-way repeated measures analysis of variance was planned, featuring three measurement points for each of the two groups. The resulting sample size was 58, and accounting for a 25% dropout rate increased the required sample size to 78 (total).

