## ***Statistical analysis***

All analyses will follow the Consolidated Standards of Reporting Trials (CONSORT) guidelines. Baseline measurements, group comparability, and descriptive characteristics will be assessed. Because patient dropout can occur for various reasons, data analyses will include both intention-to-treat (ITT) and per-protocol (PP) approaches. PP analysis considers only participants who complete the entire trial post-randomization, whereas ITT analysis includes follow-up data from all randomized participants. While PP analysis can exaggerate between-group differences, ITT analysis minimizes bias and loss to follow-up, generally producing more conservative estimates. Therefore, ITT analysis will be used as the primary method to prevent overstating effectiveness. The primary endpoint of interest is assessed after eight weeks of treatment.

All statistical analyses will be performed using IBM SPSS, version 26.0.1, with two-tailed tests ( $\alpha=0.05$ ) determining statistical significance. At baseline, categorical variables (e.g., sex, occupation, education level) will be compared between trial and control groups using chi-square tests. Continuous variables (e.g., age, BMI, pain intensity, duration of low back pain) will undergo a normality test. If the data follow a normal distribution, results will be expressed as mean  $\pm$  standard deviation (SD) and analyzed using independent-samples T-tests or Mann-Whitney U tests. Otherwise, the median (interquartile range) will be reported, and nonparametric tests will be applied. If the data meet the assumptions of homogeneity of variance and sphericity, a two-factor, three-level repeated-measures analysis of variance (group $\times$ time) will be conducted; otherwise, a mixed-effects model will be used.

According to the International Spine Conference, a two-point change in pain intensity (NRS scale: 0–10) signifies a minimum clinically important difference (MCID). Chi-square tests will compare the proportion of patients in each group who achieve MCID. Cohen's criteria will be used to evaluate the effect size across all outcome measures. No interim or subgroup analyses

are planned. An ITT approach will be used to address missing data for the primary outcome, and multiple imputation will minimize missing values.

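### The sample-size section calls 0.3 small-to-medium on Cohen's d benchmarks, but the calculation that returns 58 uses it as an ANOVA effect size, equivalent to about 0.72 to 0.83 SD at week 8

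*Protocol*

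**What the plan says.** All the inputs are in the protocol's Sample size section. It introduces Cohen's standard, under which "0.2, 0.5, and 0.8 indicate small, medium, and large effects, respectively", and continues: "A value of 0.3 was selected to represent a small-to-medium effect size". The software is G*Power 3.1.9. Alpha is 0.05, and the remaining settings are given as "power = 0.8, and a correlation among repeated" "measures of 0.5, a two-way repeated measures analysis of variance was planned", with two groups and three measurement points. The result is: "The resulting sample size was 58, and accounting for a 25% dropout rate increased the required sample size to 78 (total".

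The section does not say whether 0.3 is d, f or the partial-eta-squared version of f. It also does not say which ANOVA effect (group, time or group by time) was powered.

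The Statistical analysis section plans a group-by-time repeated-measures ANOVA, or a mixed-effects model if the assumptions fail, "with two-tailed tests" at 0.05. It adds: "The primary endpoint of interest is assessed after eight weeks of treatment".

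**The concern.** The cut-offs 0.2, 0.5 and 0.8 belong to the standardised mean difference d. A G*Power repeated-measures ANOVA takes an f-type effect size instead. For two equal groups f = d/2, so the same cut-offs on the f scale are 0.1, 0.25 and 0.4. A value of 0.3 lies between small and medium on the first scale and above medium on the second.

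If 0.3 was entered as an f-type value, the protocol describes its target effect as much smaller than the one it powered for. The statement of 80% power for a small-to-medium effect then misinforms anyone judging the design, and later anyone weighing a non-significant result. A difference the protocol would call small or medium could be missed more often than it is found.

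**Working it through.** **Inputs from the protocol.** Effect size 0.3, alpha 0.05, power 0.80, k = 2 groups, m = 3 measurements, correlation ρ = 0.5, 1:1 allocation, 25% dropout. Power comes from the noncentral F distribution with noncentrality λ.

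**Step 1: reproduce 58, taking 0.3 as an f-type value.**

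| G*Power option | λ | N needed | Check |
|---|---|---|---|
| Group × time, effect size as in SPSS | f²(N−k)(m−1) | 58 | 0.09 × 56 × 2 = 10.08; df 2, 112; power 0.808 |
| Group × time, default | f²Nm/(1−ρ) | 20 | 0.09 × 20 × 3/0.5 = 10.8; df 2, 36; power 0.812 |
| Between groups | f²Nm/(1+(m−1)ρ) | 61 (62 with equal arms) | at 62: 0.09 × 62 × 3/2 = 8.37; df 1, 60; power 0.812. At 58: power 0.785 |

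The first option returns exactly 58, and ρ does not appear in its λ. The dropout step is correct: 58/0.75 = 77.3, rounded up to 78.

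**Step 2: try 0.3 as d.** Then f = 0.15, and the three options need 218, 74 and 236 with equal arms. None gives 58. That 0.3 was entered as an f-type value is therefore an inference, but a well-supported one.

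**Step 3: express the 0.3 behind 58 in SD units at week 8.** This needs ρ, taken as the protocol's 0.5, and a profile for the group difference over baseline, week 4 and week 8. The protocol gives no profile, so two are assumed:

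- linear build-up (0, δ/2, δ), for which the default f = δ/√24;
- full effect by week 4 (0, δ, δ), for which the default f = δ/√18.

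Equating the two interaction noncentralities at N = 58 gives default f = 0.3 × √(112/348) = 0.170. Hence δ = 0.170 × 4.899 = 0.83 SD (linear) or 0.170 × 4.243 = 0.72 SD (full by week 4).

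The result depends on ρ. At 0.7 the range is about 0.56 to 0.65 SD; at 0.3 it is about 0.85 to 0.99 SD. Every value exceeds 0.5. Under the between-groups option, f = 0.3 is d = 0.6 on the mean of the three measurements, also above 0.5.

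**Step 4: power of the planned interaction test at ρ = 0.5.**

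| True week-8 difference | N analysed | Linear | Full by week 4 |
|---|---|---|---|
| 0.3 SD | 58 | 0.157 | 0.197 |
| 0.3 SD | 78 | 0.199 | 0.254 |
| 0.5 SD | 58 | 0.372 | 0.478 |
| 0.5 SD | 78 | 0.485 | 0.612 |

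For scale, 80% power at 0.3 SD would need about 430 analysed (linear) or 324 (full by week 4).

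**The case against.** The strongest reply is that the arithmetic is sound. A standard G*Power option returns 58 exactly, for the interaction that the Statistical analysis section plans to test, and the effect-size definition is the one associated with the trial's named software. The between-groups test has 78.5% power at 58, and the dropout inflation is right. All of this stands. A reader might infer that 58 cannot be obtained from the stated inputs, or that the 80% power is simply false. The protocol supports neither. For the value entered, on the scale that gives 58, power is about 80%. What fails is the description of that value, together with the listing of a correlation that the reproducing option ignores.

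A second reply is that the SD figures rest on assumed profiles and on ρ = 0.5. That is fair and they must be quoted with those conditions, but no combination examined brings 0.3 down to the protocol's medium value.

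A third is that more than 58 may be analysed, because the primary analysis is intention-to-treat with multiple imputation and outcome data are to be collected from dropouts. Hence the rows for 78; the gain is modest.

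A reader might also argue that the study cited for 0.3 tested a different contrast. With only its title to go on, nothing can be said about which of its findings was used or how, so the point does not rely on it.

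**Conclusion.** The point holds as a mislabelled effect size and an under-specified calculation, not as an arithmetic failure. On the protocol's own d scale, the 0.3 that yields 58 is larger than medium. A true week-8 difference of 0.3 SD would be detected about one time in five with 58 analysed, and at most one time in four with 78. Even 0.5 SD is below even odds with 58, and between 0.485 and 0.612 with 78.

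The conclusion rests on 0.3 being an f-type input (inferred from Step 2), on ρ = 0.5, and on the two assumed profiles. The identity of the option behind 58 is likewise inferred from reproduction, since the protocol does not name it.

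**What to change.** Keep the target of 78 and rewrite the Sample size section:

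- Delete the small-to-medium label and the 0.2/0.5/0.8 benchmarks as justification.
- Name the ANOVA effect powered and the effect-size definition that produced 58.
- Drop the correlation of 0.5 if the option used ignores it, or reconcile it with the result.
- State the detectable difference for the planned test. Possible wording: With 58 evaluable participants, the group-by-time test (0.05) has 80% power for a week-8 difference of about 0.83 SD if the effect builds linearly, or 0.72 SD if it is complete by week 4, assuming a correlation of 0.5 among repeated measures.
- Translate this into NRS and RMDQ points for a stated SD range. The protocol gives no SDs. As an illustration, an assumed NRS SD of 2 to 2.5 gives 0.72 × 2 = 1.4 to 0.83 × 2.5 = 2.1 points. The RMDQ range should be formed in the same way from an SD range that the sponsor justifies.

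A smaller detectable difference, 0.65 SD at 80% power with 58, is available from a baseline-adjusted week-8 comparison (correlation 0.5). It may be quoted only if that comparison also becomes the primary analysis in the Statistical analysis section. At 0.65 SD the currently planned interaction test has only 58% (linear) to 71% (full by week 4) power.

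The cost is the rewording of one section, with no extra participants. The downside is that the stated detectable effect becomes less favourable.
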